### Interventions and Control

Participants randomized to the intervention (ie, telemedicine) arm will receive an internet-based support program for smoking cessation using the CASC. In contrast, participants randomized to the control (face-to-face) arm will receive the conventional face-to-face standard smoking cessation support program, also using the CASC.

The standard smoking cessation support program in Japan consists of 5 clinic visits over 12 weeks, including doctor consultation and exhaled CO check at a registered institution or clinic [5]. All study participants will meet their primary care physicians face to face during the first visit to ensure that they fully understand the study protocol. On this first visit, the physicians will decide on the appropriate treatment drug, provide guidance in accordance with the standard program procedure, and provide participants with the CASC. Following the first visit, control patients are supposed to visit the clinic in weeks 2, 4, 8, and 12, and at each visit, their primary doctors will administer the treatment drug.

Patients in the telemedicine arm will undergo the standard smoking cessation support program with the CASC. However, instead of visiting the clinics, they will meet their physicians to receive counseling via a video-conference system and a standardized telemedicine platform app, in accordance with the guideline for telemedicine in Japan [22]. As in the standard procedure, they will meet with their physicians via internet at each of the planned visits (2, 4, 8, and 12 weeks).

The CASC consists of the following: (1) a CASC smartphone app for patients with nicotine dependence, (2) a mobile CO checker for patients, and (3) a Web-based patient management software for health care providers [20]. Participants are asked to watch a 5- to 10-min lecture on smoking cessation every day (see Multimedia Appendix 3 for the specifics). They are also asked to write a short comment as a diary and to check their exhaled CO concentration with the device. Primary care physicians can monitor their diaries, physical conditions, lecture progress, and exhaled CO concentration data.

The CASC will be delivered by the study sponsor, CureApp Inc, Tokyo, Japan, and will be carefully managed to avoid being used outside the current study at each institution or clinic. A prescription code specific to each practicing institution or clinic is required to activate the entire system issued by the sponsor, and the sponsor regularly (at least once a year) performs an inventory and confirms the devices are not used outside the research.

### Endpoints

The primary endpoint of this study will be the CAR from weeks 9 to 12. We hypothesize that the telemedicine group will not show clinically worse CAR from weeks 9 to 12 than the control group (threshold of 15%). The CAR is defined as the percentage of individuals continuously not smoking during the specified period. We will also evaluate the following secondary endpoints: (1) smoking cessation success rate at the points of 4, 8, 12, and 24 weeks; (2) CAR from weeks 9 to 24; (3) changes in the scores on the mood and physical symptoms scale (MPSS) [24] and 12-item French version of the Tobacco Craving Questionnaire (FTCQ-12) [25]; (4) Kano Test for Social Nicotine Dependence (KTSND) score [26] at 8, 12, and 24 weeks; (5) time to first lapse after the first visit; (6) nicotine dependence and cognition scale (NDCS) score at 12 and 24 weeks; (7) usage rate of the CASC; (8) qualitative questionnaire about the usability and acceptability of telemedicine; and (9) the presence of product problems or adverse events.

The NDCS is a scale for measuring nicotine dependence and cognitive impairment among smokers. It consists of 8 items, each rated on a 4-point scale (ranging from 0 to 3). A higher total score (minimum=0, maximum=24) implies more severe dependency or cognitive impairment.

### Follow-Up Schedule and Data Collection

The follow-up schedule is shown in Table 1. Follow-up visits will be conducted in each clinic. At the registration visit, we will record patients’ baseline profile, Tobacco Dependence Screening Test [27], BI, Fagerström test for nicotine dependence [28], FTCQ-12, KTSND, MPSS, NDCS, exhaled CO concentration, and smoking cessation status. The baseline profile will consist of age, gender, body weight, years of smoking, number of cigarettes per day, and past medical history. We will check their FTCQ-12, KTSND (after 8 weeks), MPSS, NDCS (after 12 weeks), exhaled CO concentration, smoking status, the frequency of application usage and presence of product problems, or adverse events at 2 weeks (±1 week), 4 weeks (±1 week), 8 weeks (±2 weeks), 12 weeks (±2 weeks), and 24 weeks (±4 weeks). The qualitative questionnaire about the usability and acceptability of telemedicine will be asked only for the participants in the telemedicine arm at 24 weeks. Each doctor at the study site will be responsible for the case report form, and the monitoring staff, who are employees of the sponsor, will visit each study site and check the data quality during the study period.

### Statistical Methods

We will compare all endpoints between the telemedicine and the face-to-face arms. Baseline characteristics will be described by means and standard deviations, or medians and interquartile ranges (for continuous variables), or proportions (for categorical variables). We will analyze the primary outcome using the full analysis set (excluding participants who violate the abovementioned inclusion or exclusion criteria). For all outcomes, summary statistics and group difference measures (eg, odds ratios and mean differences) will be presented with 95% CIs and *P* values from 2-sided tests (eg, logistic regression and analysis of covariance).

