## Methods

### Study Design

This study will be a randomized, controlled, open-label, multicenter trial. The study will be conducted in 4 community clinics located in Tokyo, Japan: Tokyo-Eki Center-building Clinic, Shinjuku Research Park Clinic, Fukuwa Clinic and Miyazaki RC Clinic. Figure 1 provides an outline of the trial.

Participants in both arms will undergo the smoking cessation support program used in Japan. For the telemedicine arm, the entire program will be conducted remotely via an internet-based video system except for the first registration visit [22], whereas participants in the control arm will follow the standard program in the face-to-face manner. Participants in both arms will be asked to download the CASC smartphone app as well as be given a mobile CO checker. These will be used for 24 weeks. The follow-up schedule is shown in Table 1.

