### Participants

We will recruit nicotine-dependent but otherwise healthy adults from March to July 2018. We plan to follow them up until January 2019 (ie, for 24 weeks). We will include the participants who are diagnosed as nicotine dependent, have smoking history of Brinkman index (BI) >200, and have a determination to quit smoking immediately. Then, we will exclude those participants with severe mental illness and those with any smoking cessation aid, besides prescribed medication at clinics before or after enrollment, based on the subjective questionnaire on the enrollment visit (detail of the inclusion criteria is shown in Multimedia Appendix 1, and the exclusion criteria is shown in the Multimedia Appendix 2). Not-Burning-Tobacco product users can be included if the participant meets the inclusion criteria of the BI, which was defined as the number of combustible traditional tobacco packs per day multiplied by the number of smoking years. Primary doctors at each study site will obtain written informed consent from all study participants, and the consent forms that will be used have been approved by our institutional review board. We will inform all participants that their medical care will not be affected if they refuse to be enrolled in the trial. In addition, participants will be able to drop out of the study at any time. Clinics participating in this study can provide the smoking cessation support program and have the necessary equipment to conduct telemedicine (eg, Wi-Fi access in the facility).

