### Sample Size

As shown in the findings of a previous pilot study of the CASC, the difference in CAR from weeks 9 to 12 between using a CASC smartphone app group (78%) and historical control groups (not using the application; 54%) is 24% [21,23]. Accordingly, we assumed that the treatment effect of both arms using the CASC in the current study will be 80% and the threshold amount should be 15%, which is smaller than the difference between the CASC group and historical control group in the previous study. The sample size was calculated as 114 (57 per arm) based on the precision of the estimate that the lower limit of the 95% CI of the difference between treatment effects exceeded the threshold amount of 15%. Therefore, we aim to recruit at least 114 participants to allow for this sample size.

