### Randomization

For randomization, we will use the block randomization method (with 4 blocks) with a 1:1 allocation ratio. Participants will be allocated in this way to either the intervention (telemedicine) or control (face-to-face) arm. The randomization will be performed at the time of participants’ registration by a staff member using a computer-generated random sequence for each participating clinic.

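### The primary analysis set drops participants who breach the eligibility criteria, and one criterion is worded to include cessation-aid use after enrolment, so randomised participants could be removed for later behaviour

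*Protocol article*

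**What the plan says.** Statistical Methods (protocol article) analyses the primary outcome "using the full analysis set (excluding participants who violate the abovementioned inclusion or exclusion criteria"). The criteria it points back to are in the Participants section, which excludes "those with any smoking cessation aid, besides prescribed medication at clinics before or after enrollment" and adds that this is "based on the subjective questionnaire on the enrollment visit". The detailed exclusion criteria are in Multimedia Appendix 2, of which only the title is available.

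On timing, the Randomization section states: "The randomization will be performed at the time of" participants' registration. Table 1 places registration on Day 1. On blinding, Study Design says: "This study will be a randomized, controlled, open-label, multicenter trial". Under Follow-Up Schedule and Data Collection, the doctor at each site is responsible for the case report form.

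The Endpoints section hypothesises that "the telemedicine group will not show clinically worse CAR from weeks 9 to 12 than the control group (threshold of 15"%). The article does not use the term non-inferiority, but the structure is the same.

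**The concern.** A criterion that reaches past enrolment is no longer purely an eligibility criterion. Because randomisation is at registration, use of another aid after enrolment happens after randomisation. An analysis rule that drops everyone who violates the criteria, without limiting this to breaches present at randomisation, then allows people to leave the primary comparison because of what they did during treatment.

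Seeking another aid may be related to struggling to quit, which is the endpoint itself. The mode of contact differs between arms, so use of aids, or its detection, could differ too. Participants and site doctors know the allocation. If those removed are mainly failures, the continuous abstinence rate (CAR) rises in each arm by an amount that depends on how many failures that arm has and what share is removed. The comparison is then no longer the randomised one.

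**Working it through.** **Inputs from the article.** 57 per arm; CAR assumed to be 80% in both arms; threshold 15 points; 95% confidence interval (Sample Size).

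**Assumed inputs.** The fraction e of failures removed in each arm, and a true CAR of 65% v 80%, which lies exactly on the threshold. The article gives no figure for either.

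**1. The plan's own sample size.** Setting the half-width to 15 points gives n per arm = 2 × 0.8 × 0.2 × (z/0.15)².
- z = 2: 0.32 × (2/0.15)² = 56.9, rounded up to 57 per arm, or 114 in total. This matches.
- z = 1.96: 54.6, rounded up to 55 per arm, close to the stated figure.

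At 57 per arm the half-width is 1.96 × √(0.32/57) = 14.7 points. The slack against the threshold is 0.3 points.

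**2. Shift in the expected difference.** If a fraction e of failures is removed, the expected CAR becomes p / (1 − e(1 − p)).

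| Share of failures removed (telemedicine v control) | Telemedicine | Control | Difference (points) |
|---|---|---|---|
| None | 0.650 | 0.800 | −15.0 |
| 30% v 30% | 0.65/(1 − 0.3 × 0.35) = 0.726 | 0.80/(1 − 0.3 × 0.20) = 0.851 | −12.5 |
| 30% v 10% | 0.726 | 0.80/(1 − 0.1 × 0.20) = 0.816 | −9.0 |
| 10% v 30% | 0.65/(1 − 0.1 × 0.35) = 0.674 | 0.851 | −17.7 |

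In people, 30% of telemedicine failures is 0.3 × 0.35 × 57 ≈ 6, and 10% of control failures is 0.1 × 0.20 × 57 ≈ 1.

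**3. Chance of a false conclusion of not clinically worse.** Simulation of 1,000,000 trials, 57 per arm, true CAR 65% v 80%, Wald 95% interval, success if the lower limit is above −15 points.

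| Share of failures removed | Telemedicine arm only | Same share in both arms |
|---|---|---|
| 0% | 2.7% | 2.7% |
| 10% | 5.1% | 3.3% |
| 20% | 9.2% | 4.2% |
| 30% | 16.1% | 5.6% |

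Equal shares inflate the error modestly, because the arm with more failures loses more of them. The larger figures need removal that differs by arm.

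**4. One removal in a single data set.** Lower limit = p₁ − p₂ − 1.96 × √(p₁(1 − p₁)/n₁ + p₂(1 − p₂)/n₂).
- 45/57 v 46/57: difference −1.8 points, lower limit −16.5. The threshold is not met.
- 45/56 v 46/57, with one telemedicine failure removed: lower limit −14.95. The threshold is met.

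**The case against.** The strongest reply is that the criterion is a baseline one. The article ties it to the questionnaire at the enrolment visit, and a Day 1 questionnaire can record past, current or planned use but not what happens later. Neither Table 1 nor the follow-up section lists other-aid use among the items collected, so nothing shown says how later use would reach the analysis set. The full wording is in an appendix that is not available. On this reading, only people ineligible at registration are removed.

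This reply lowers the certainty but does not remove the point. The criterion's wording still extends past enrolment, which a Day 1 questionnaire cannot establish as actual use. The analysis rule does not limit removal to breaches present at randomisation.

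A reader might infer three stronger things that the document does not support:
- **That removal for later aid use will happen.** It is permitted by the wording, not shown to be intended.
- **That the bias favours telemedicine.** The article does not say which arm would use other aids more. If control participants were removed more often, the bias could run the other way, as the 10% v 30% row shows. Nor is every aid user a failure: one who was abstinent would be removed as a success.
- **That losing three people per arm breaks the stated precision.** With CAR held at 80%, 54 per arm gives a half-width of 15.1 points. But the mechanism at issue removes failures, which raises CAR: 45.6/54 = 84.4%, with half-width 1.96 × √(2 × 0.844 × 0.156/54) = 13.7 points, narrower than 14.7. The risk is bias, not lost precision.

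The article's silence on further analysis sets is not a fault either, since a condensed article commonly leaves them to the full protocol or analysis plan.

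**Conclusion.** The point holds as a defect in a stated rule. Read together, Participants and Statistical Methods allow randomised participants to be removed from the primary analysis for aid use after randomisation, in an open-label trial whose claim is that telemedicine is not clinically worse. It should be fixed; confidence is moderate, because the enrolment-questionnaire clause and the unseen appendix leave the intended meaning open.

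The size is illustrative. It assumes that those removed are failures, a true difference on the threshold, and removal shares that the document does not supply. What rests on the plan's own figures is the small slack of 0.3 points, which explains why a single removal can be enough to change the conclusion.

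**What to change.** Reconcile the Participants and Statistical Methods sections:
- Analyse the primary outcome in all randomised participants. Exclude only those shown by data recorded before randomisation, and reviewed without knowledge of arm or outcome, never to have been eligible.
- For analysis purposes, restrict the aid criterion to use at or before enrolment.
- Keep participants who use another aid later in the primary analysis with their observed smoking status.
- Move their exclusion to a supportive per-protocol analysis.

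The cost is about one paragraph of analysis wording, to be settled before outcomes are compared by arm. The sample size stays at 114 and enrolment is unaffected. A small downside is that observed CARs may be slightly lower.

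### The only stated success criterion has the wrong sign, and the analysis section does not carry the 15-point difference criterion into the primary analysis

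*Protocol article*

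**What the plan says.** Three sections of the protocol article bear on the primary comparison.

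- **Endpoints** gives the hypothesis: "We hypothesize that the telemedicine group will not show clinically worse CAR from weeks 9 to 12 than the control group (threshold of 15" per cent. The direction is given in words and the size as a number.
- **Sample Size** sets the scale and the criterion. The threshold is chosen against a 24-point difference (78% v 54%): "the threshold amount should be 15%, which is smaller than the difference between the CASC group and historical control group in the previous study". The planning assumption is that "we assumed that the treatment effect of both arms using the CASC in the current study will be 80" per cent. The size is then given: "The sample size was calculated as 114 (57 per arm) based on the precision of the estimate", the requirement being that "the lower limit of the 95% CI of the difference between treatment effects exceeded the threshold amount of 15" per cent.
- **Statistical Methods** covers all outcomes in one sentence: "group difference measures (eg, odds ratios and mean differences) will be presented with 95% CIs", together with P values from 2-sided tests. Logistic regression and analysis of covariance are the example tests. The section does not mention the 15% threshold, a difference in proportions, or a rule that compares a confidence limit with the threshold.

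**The concern.** The hypothesis is non-inferiority in substance, although the article does not use that term. Such a hypothesis is judged by whether a confidence limit for the treatment difference stays on the right side of a margin. Two things stand in the way.

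First, the one place that states such a rule gives it with the wrong sign. Read literally, telemedicine would have to be more than 15 points better. If the difference were taken as face-to-face minus telemedicine, the literal rule would require telemedicine to be more than 15 points worse. Neither matches the hypothesis.

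Second, the analysis section does not repair this. For a binary outcome, the measure and method it names are the odds ratio and logistic regression, which are on another scale from the threshold. The usual P value from that model tests no difference.

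At stake is the trial's main conclusion. A report that kept to the named examples could give an odds ratio and a P value without applying the 15-point rule, and a non-significant P could then be mistaken for support of the hypothesis.

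**Working it through.** **Inputs.** From Sample Size: 80% CAR in both arms, threshold 15 points, 95% CI, 57 per arm. From Statistical Methods: odds ratio, logistic regression, 2-sided P. Assumed here for illustration: a true 65% v 80%, the 38/57 v 46/57 result, and control rates other than 80%.

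**1. Reproducing 57 per arm.** Take the smallest n at which the 95% CI half-width for 80% v 80% is below 0.15, so that the lower limit lies above -0.15.

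- Normal approximation: n = 1.96² × 2 × 0.8 × 0.2 / 0.15² = 54.6, so 55 per arm. Newcombe's interval also gives 55.
- t quantile with n - 1 in the variance: half-width = t × √(0.32/(n - 1)). This is 0.1512 at n = 56 and 0.1498 at n = 57, so exactly 57 per arm.

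The plan's figure therefore follows from a limit of -15 points.

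**2. The criterion as printed.** At 80% v 80% with 57 per arm, SE = √(0.32/57) = 0.0749.

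- Lower limit above +0.15: Φ(-0.15/0.0749 - 1.96) = 0.00004 (exact binomial enumeration 0.00005).
- Lower limit above -0.15: Φ(0.15/0.0749 - 1.96) = 0.52 (exact 0.53).

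Under the plan's own assumption the printed rule would almost never be met. Whether 52% is adequate is a separate question.

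**3. The threshold on the odds-ratio scale.** For control rate p, OR = [(p - 0.15)/(1 - p + 0.15)] / [p/(1 - p)].

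| Control CAR | OR for a 15-point loss |
|---|---|
| 50% | 0.538 |
| 60% | 0.545 |
| 65% | 0.538 |
| 70% | 0.524 |
| 80% | 0.464 |
| 90% | 0.333 |

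No single odds ratio corresponds to 15 points. Even with the control rate known to be 80%, the scales can disagree. At 80% v 80%, SE(log OR) = √(2/(57 × 0.16)) = 0.468, so the expected CI is exp(±1.96 × 0.468) = 0.40 to 2.50. Its lower limit is below 0.464, although the risk-difference limit (-0.147) just clears -0.15. By exact enumeration (0.5 added to each cell for the OR), the OR limit clears 0.464 about 38% of the time, and the risk-difference limit clears -15 points about 53% of the time.

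**4. What a two-sided test of no difference shows.** Suppose the truth is 65% v 80%.

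- SE = √((0.2275 + 0.16)/57) = 0.0824 and power = Φ(0.15/0.0824 - 1.96) ≈ 0.44. By exact enumeration the test is non-significant 56% of the time.
- The rule of lower limit above -15 points would wrongly pass about 2.7% of the time.

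**5. An illustrative result.** Telemedicine 38/57 (66.7%), face-to-face 46/57 (80.7%).

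- Difference -14.0 points; SE = √(0.2222/57 + 0.1557/57) = 0.0814; 95% CI -30.0 to +1.9.
- Pooled test: z = 0.1404/0.0825 = 1.70, P = 0.089.

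The P value is above 0.05, yet the interval reaches twice the threshold.

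**The case against.** The strongest reply is that the three sections should be read together. The odds ratio and logistic regression are introduced as examples in a sentence that covers every outcome, so a risk difference is not excluded, and 95% CIs are promised throughout. Sample Size already names the lower limit of the 95% CI of the difference and the 15% threshold. The intended sign is clear from the repeated aim of not being clinically worse and from the reproduced sample size. The study is described as proof of concept, and an analysis plan that is not shown may fix the estimator.

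Much of this stands, and it rules out stronger readings that a reader might infer:

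- **That the planned analysis cannot answer the question.** The lists are not exclusive, and a usable criterion exists once its sign is put right.
- **That two-sidedness is a fault.** The lower limit of a two-sided 95% CI is a one-sided 2.5% non-inferiority test.
- **That Endpoints is also wrongly signed.** It gives direction in words and an unsigned size, which is coherent.
- **That the authors will read a non-significant P as success.** The article does not say so; the calculation shows only what such a reading would cost.
- **That a particular interval method is required.** That is a preference, and commonly left to the analysis plan.

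What the reply does not remove is that the printed criterion is wrong, and that the section governing the analysis points to another scale without linking back to the criterion. Leaving the primary measure to examples also leaves the scale open to choice after the data are seen, and step 3 shows that this choice can change the conclusion.

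**Conclusion.** The point holds in this form. The stated criterion needs a minus sign: 57 per arm is reproduced at -15 points (55 by the normal approximation, 57 with the t quantile), and the literal criterion would be met with probability of about 0.00005 under the plan's own assumption. Statistical Methods does not apply the criterion, and the odds ratio it names cannot be read directly against a 15-point difference. A non-significant two-sided P is not evidence for the hypothesis, since it would occur about 56% of the time if telemedicine were truly 15 points worse.

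This rests on reading 15% as percentage points, which its comparison with the 24% difference supports, and on 57 analysed per arm. The 56% also assumes 65% v 80% and a conventional test of no difference, which the article implies by naming logistic regression and P values but does not spell out. It is a fault of wording and specification, not of the data to be collected, but it bears on the trial's main conclusion.

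**What to change.** - **Sample Size:** state the criterion as the lower limit of the 95% CI for the difference in CAR weeks 9 to 12, telemedicine minus face-to-face, lying above -15 percentage points.
- **Statistical Methods:** name that risk difference with its two-sided 95% CI as the primary analysis. Conclude that telemedicine is not clinically worse only if the lower limit is above -15 points. Keep the odds ratio and P value as supportive, and say that a non-significant P does not establish the hypothesis.
- **Endpoints:** add only that the threshold is in percentage points.

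The cost is a few sentences, with no added data or patient burden. Recruitment is reported as complete and the trial is open-label, so the change should be made and dated before the primary outcome is analysed.
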